## Methods

### Study design

This is a three-arm, open-label non-inferiority randomized controlled clinical trial that will be conducted at the National Ayurveda Teaching Hospital in Colombo, Sri Lanka. TMD12, used in traditional Ayurveda, and its freeze-dried formulation will be the test products. The efficacy and safety of the two Ayurvedic dosage forms will be tested against the antihistamine loratadine. Patients with symptoms of AR will be allocated randomly into the three arms after a 1-week run-in period and the medications given orally for 28 days. This study protocol was developed as required by the Standard Protocol Items: Recommendations for Interventional Trials (SPIRIT) (Additional file 1).

Ethics approval has been obtained from Ethics Review Committee, Institute of Indigenous Medicine (ERCIIM), University of Colombo, Sri Lanka (ERC 18/76) and the Ethics Committee of the Faculty of Medicine, University of Colombo, Sri Lanka (EC-18-090). The trial was registered in the ISRCTN registry (Trial number ISRCTN18149439) (Additional file 2).

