### Sample size

Sample size was calculated based on the primary outcome measurement of TNSS and as for a non-inferiority clinical trial. This study is designed to evaluate the comparative clinical efficacy and safety of two Ayurvedic dosage forms with the antihistamine loratadine, assuming non-inferiority-between the three interventions. Sample size was calculated as specified by Hampel et al. [11]. According to a previous study done among patients with allergic rhinitis using loratadine, clinically significant standardized effect sizes of TNSS are reported in the range of 0.57 to 0.67 [11]. Therefore, a standardized effect size of 0.5 was considered as the non-inferiority margin using the effect reported by Hampel and team.

Sample size was calculated for a significance level (**α**) of 5% and power of 80%. The sample size calculated using these values is 64 per group. With an expected dropout rate of 10%, minimum sample size was calculated as 70 for one arm.

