## Method of data analysis

For primary and secondary outcome measures, the mean values at baseline and at the end of the study and the mean differences will be compared between the three arms using ANOVA (analysis of variance) or the non-parametric Kruskal–Wallis test, depending on the normality of the data. Within each treatment arm, the difference in primary and secondary outcome measures before and after the intervention period will be compared using paired-sample *t* test or non-parametric Wilcoxon signed-rank test, depending on the normality of the data. 95% confidence intervals will be calculated for all outcome measures that are normally distributed. Categorical variables will be compared between groups using the Chi-square test. Possible confounders will be adjusted using ANCOVA. Following adjustment for confounding using ANCOVA, adjusted mean values with confidence intervals will be calculated and reported. Statistical analysis will be performed using the SPSS Statistical Package program (ver. 18.0), and the level of significance will be established at α = 0.05. Missing data at outcome assessment will be replaced with the available latest values of the outcome measure. Intention-to-treat analysis will be performed for all efficacy outcomes and safety outcomes. In addition, per-protocol analysis will be performed for the efficacy outcomes by including only the patients completing the follow-up.

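### The only stated between-arm method that could apply to adverse-event proportions is a Chi-square test with no interval, so the comparative safety aim gets no bound on excess harm

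*Protocol article*

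**What the plan says.** Safety is part of the comparison with loratadine. The Study design section says "The efficacy and safety of the two Ayurvedic dosage forms will be tested against the antihistamine loratadine", and the Abstract gives the same aim. The Sample size section describes the trial as "designed to evaluate the comparative clinical efficacy and safety of two Ayurvedic dosage forms with the antihistamine loratadine, assuming non-inferiority-between the three interventions". The only margin given there is for the Total Nasal Symptom Score (TNSS), at a standardised effect of 0.5, and the 70 patients per arm follow from it.

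The Safety assessment section has adverse events recorded weekly and laboratory tests done before and after treatment. The Method of data analysis section puts safety outcomes on an intention-to-treat basis. The statements there that bear on comparing them are:

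- for categorical data: "Categorical variables will be compared between groups using the Chi-square test";
- for intervals: "95% confidence intervals will be calculated for all outcome measures that are normally distributed";
- after ANCOVA: "adjusted mean values with confidence intervals will be calculated and reported";
- for all tests: "the level of significance will be established at α = 0.05".

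The article gives no expected adverse-event rate, no safety margin and no power statement for safety.

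**The concern.** Whether a patient had an adverse event is a yes/no variable, so of the stated between-arm methods only the Chi-square rule fits it. That test asks whether rates differ. It gives no estimate of how much more harm a herbal product might cause, and no upper limit on it. Neither interval rule covers a proportion: one is tied to normality and the other to adjusted means.

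The Background section says that no published study has evaluated the efficacy and safety of the decoction, so this trial's safety comparison may be the first that readers have. With a sample sized on TNSS alone, a non-significant result could sit beside a large true excess of events, and a p-value would not show that.

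**Working it through.** **Inputs from the article.** 64 evaluable and 70 randomised per arm; α = 0.05, taken as two-sided because no side is stated; 1:1:1 allocation; intention-to-treat for safety, so 70 per arm is the relevant number. **Assumed input.** The loratadine event rate, varied because the article gives none.

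**1. The article's own figure.** For a standardised difference of 0.5, two-sided 5% and 80% power, n = 2(1.960 + 0.842)²/0.5² = 62.8, so 63 by the normal approximation. The t-based calculation gives 63.8, so 64, as stated. This calculation uses TNSS only.

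**2. Power of a pairwise Chi-square test at 70 per arm.** The normal approximation is

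power = Φ{ [ |p₂ − p₁|√n − 1.960√(2p̄(1 − p̄)) ] / √( p₁(1 − p₁) + p₂(1 − p₂) ) }, with p̄ = (p₁ + p₂)/2.

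For 5% vs 15%: (0.10 × 8.367 − 1.960 × 0.4243)/0.4183 = (0.8367 − 0.8315)/0.4183 = 0.012, so power is 0.505. Exact enumeration of all pairs of binomial counts, with Pearson's statistic and no continuity correction, gives 0.524. The exact miss rates (1 − power) are:

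| Loratadine vs herbal | Change | Missed |
|---|---|---|
| 1% vs 3% | tripling | 92% |
| 2% vs 6% | tripling | 79% |
| 3% vs 9% | tripling | 68% |
| 5% vs 15% | tripling | 48% |
| 7% vs 21% | tripling | 32% |
| 10% vs 30% | tripling | 14% |
| 20% vs 60% | tripling | under 1% |
| 5% vs 10% | doubling | 80% |
| 10% vs 20% | doubling | 62% |

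**3. Sensitivity to the form of the test, at 5% vs 15%.** With Yates' correction or Fisher's test, 59% are missed. A single three-arm test on 2 degrees of freedom (simulated) misses 43% if one herbal arm triples and 51% if both do. For 80% power, the pairwise test needs (1.960 × 0.4243 + 0.842 × 0.4183)²/0.10² = 140.1, so 141 per arm.

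**4. What an interval would show.** The Newcombe interval for d = p₂ − p₁ uses the Wilson limits (l, u) of each arm:

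lower = d − √[(p₂ − l₂)² + (u₁ − p₁)²]; upper = d + √[(u₂ − p₂)² + (p₁ − l₁)²].

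The counts below are illustrative.

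- **4/70 vs 4/70.** Each arm is 5.7%, with Wilson limits 2.2% to 13.8%. The half-width is √(0.0808² + 0.0347²) = 0.088. The difference is 0, with interval −8.8 to +8.8 percentage points; Chi-square p = 1.0. The score interval for the risk ratio is 0.28 to 3.5, so even equal counts do not exclude a tripling.
- **10/70 herbal vs 4/70 loratadine.** 14.3% (7.9% to 24.3%) against 5.7%. The difference is 8.6 points, with interval −1.7 to +19.2; p = 0.09. The result is non-significant, yet compatible with an excess of 19 points.

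**The case against.** The strongest reply is that this is one condensed paragraph of a journal article. Risk differences, intervals for proportions and adverse-event tables are commonly left to a full protocol or analysis plan, neither of which is shown. The Chi-square sentence is general and does not name adverse events, and the interval sentence says when intervals will be produced without forbidding others. Sizing on the primary efficacy outcome is normal practice. Safety is also watched through weekly recording, a provision for early termination and an independent three-member board. Intervals would add no power.

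Much of this stands, and it limits the point. Several stronger readings are tempting and are not supported:

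- A reader might infer that the trial will declare comparable safety whenever p exceeds 0.05. No sentence says so, the margin is for TNSS only, and a significant result with fewer events on a herbal product would favour that product more strongly.
- A reader might infer that the test misses a tripling about half the time in general. That holds only near an assumed 5% loratadine rate.
- A reader might infer a single three-arm test that cannot say which product differs. The article writes only of comparison between groups, which does not exclude pairwise tests.
- A reader might treat the laboratory safety results as yes/no outcomes. The Safety assessment section does not define them so, and continuous values could fall under the existing interval rule.

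What the reply does not remove is that the article names a method and ties its general interval rule to normality. That condition is unnecessary, because valid intervals for proportions exist, and the named test cannot bound excess harm.

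**Conclusion.** The point holds as a modest, inexpensive improvement. A comparative safety aim is paired with a stated test that gives no bound on excess harm, and the stated interval rules do not reach proportions. Non-significance at 70 per arm could not support a claim of comparable safety for less common events. Across assumed loratadine rates of 1% to 10%, a tripling is missed between 92% and 14% of the time. At 10% or more a tripling is usually detected, but a doubling from 10% to 20% is still missed 62% of the time. These figures rest on the assumed rates, a two-sided 5% level, 70 analysed per arm and an uncorrected pairwise test. They describe what the stated method could support, not a conclusion that the article says it will draw.

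**What to change.** In the Method of data analysis section:

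1. For each herbal product against loratadine, report the risk difference with a 95% confidence interval (for example the Newcombe score interval) for patients with any adverse event and for any other binary safety outcome.
2. Drop the restriction of confidence intervals to normally distributed outcomes.
3. State that a non-significant Chi-square test will not be taken as evidence of comparable safety.

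This needs a few sentences and one extra table, with no new patients or data. The price is a more modest safety statement, since the intervals will be wide at this sample size. The change makes the remaining uncertainty visible but does not reduce it.

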### Baseline assessment

Nasal symptoms (watery rhinorrhea, nasal obstruction, sneezing, nasal itching), non-nasal symptoms, HRQoL, hematological and biochemical investigations (IgE level, FBS, FBC, ESR, ALT/AST, serum creatinine, UFR) will be assessed at baseline.

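### The TNSS comparison is unadjusted and switches to a rank test on non-normality, which gives no mean-difference interval to set against the margin; one baseline-adjusted ANCOVA should be fixed as primary

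*Protocol article*

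**What the plan says.** All references are to the protocol article.

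- **Method of data analysis.** For primary and secondary outcomes, values at baseline and at the end of the study, and mean differences, are compared across the three arms by ANOVA or Kruskal–Wallis, "depending on the normality of the data". Confidence intervals at 95% are promised for outcomes that are normally distributed. Then: "Possible confounders will be adjusted using ANCOVA", with adjusted means and their intervals to be reported. No covariate is named and no analysis is labelled primary.
- **Baseline assessment.** Nasal symptoms, among other measures, "will be assessed at baseline", so the covariate exists for every patient.
- **Sample size.** The trial is sized for non-inferiority: "a standardized effect size of 0.5 was considered as the non-inferiority margin". The calculation uses no covariate.
- **Inclusion criteria and Primary outcome.** TNSS runs from 0 to 12 and entry requires a score above 6, which limits baseline to 7–12.

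**The concern.** There are three linked problems, the first being the most serious.

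1. **The switch can remove the estimate that the design needs.** A non-inferiority conclusion rests on a confidence interval for a difference, compared with the margin. ANOVA concerns means and Kruskal–Wallis concerns ranks. If normality is rejected, the between-arm comparison becomes a rank test with no mean-difference interval, and the promise of unadjusted intervals lapses as well. What is estimated then depends on the data.
2. **Several candidate results and no primary one.** End values, mean differences, ranks and adjusted means are all planned. In an open-label trial it should be settled in advance which of them decides the question.
3. **The reason given for adjustment is not the useful one.** Randomised arms have no systematic confounding. Baseline TNSS belongs in the model because it is likely to predict day-28 TNSS and so narrows the interval.

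**Working it through.** **Inputs from the protocol.** Significance level "of 5% and power of 80"% (sidedness not stated); analysis level 0.05; margin 0.5 SD; "The sample size calculated using these values is 64 per group"; 70 per arm with 10% dropout. The protocol does not give the correlation r between baseline and day-28 TNSS, the ratio k of baseline SD to day-28 SD, or whether the margin's SD is that of end values or of changes. The power figures below take the margin in day-28 SD units.

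**Step 1: reproduce the stated size.** With a true difference of zero and one-sided 2.5%, n = 2 × (1.960 + 0.842)² / 0.5² = 62.8, so 63 per arm. The exact noncentral-t calculation gives 64, with power 80.1%. One-sided 5% would give 50 (normal) or 51 (t). The stated 64 is therefore an unadjusted pairwise comparison at one-sided 2.5%.

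**Step 2: effect of adjusting for baseline.** Relative to end values (variance 1), ANCOVA has variance 1 − r². In the normal approximation, power = Φ(0.5 × √(64/2) / √(1 − r²) − 1.960).

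- Unadjusted: Φ(2.828 − 1.960) = 80.7%.
- r = 0.3: Φ(2.828/√0.91 − 1.960) = 84.3%.
- r = 0.5: Φ(2.828/√0.75 − 1.960) = 90.4%.

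Exact-t power at 64 per arm, with one degree of freedom charged for the covariate:

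| r (assumed) | End value, unadjusted | ANCOVA | ANCOVA n per arm equivalent to 64 |
|---|---|---|---|
| 0 | 80.1% | 80.1% | 64 |
| 0.2 | 80.1% | 81.7% | 62 |
| 0.3 | 80.1% | 83.7% | 59 |
| 0.5 | 80.1% | 90.0% | 48 |
| 0.7 | 80.1% | 97.6% | 33 |

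At 63 per arm (70 less 10%), the unadjusted figure is 79.5%, and ANCOVA gives 83.1% at r = 0.3 and 89.5% at r = 0.5. The lost degree of freedom costs less than 0.1 point.

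**Step 3: change scores.** Their relative variance is 1 + k² − 2rk, which equals (1 − r²) + (k − r)². It is never below the ANCOVA variance, but the gap depends on k. At r = 0.3 it is 1.4 if k = 1 and 1.0 if k = 0.6, against 0.91 for ANCOVA.

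**Step 4: would the switch be triggered?** The protocol does not say how normality will be judged, so this is illustrative only. The assumptions were:

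- 64 per arm and r = 0.4;
- baseline mean 9 and SD 1.5, rounded and held to 7–12;
- day-28 SD 2.5 and mean 3, 4 or 5, rounded and held to 0–12;
- Shapiro–Wilk at 5% in each arm, with any rejection leading to the rank test.

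The rank branch was taken in 100%, 97% and 67% of simulated trials on end values, and in 90%, 79% and 69% on change.

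**The case against.** The case on the other side has several good points.

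- **Unadjusted ANOVA is valid in a randomised trial**, and the stated sample size is met without a covariate. This stands: omitting baseline loses efficiency but is not an error.
- **ANCOVA with intervals for adjusted means is already planned**, and an analysis plan that is not shown may name baseline TNSS as a covariate. This stands in part. An absent covariate list is no fault in an article. The switch, however, is stated text that an analysis plan would have to reverse, and nothing ties the adjusted means to the margin as the deciding result.
- **The gain rests on an r that is not given.** This stands. The entry rule restricts the baseline range and may lower r; at r = 0.2 or below the gain over end values is under 2 points.
- **The power figures are not for the written test.** This also stands. They describe a pairwise comparison with the margin, whereas the section specifies a three-arm test of difference.

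A reader might infer that confounders will be picked after the data are seen. The text does not say when or how they are chosen, so that charge is not supported. A reader might also infer that change scores would cost a large, definite amount of power. That needs equal baseline and day-28 SDs, which the entry rule makes doubtful, and it needs the margin to be in end-value SD units, which the protocol does not say.

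**Conclusion.** The point holds as a recommended change. What the document itself establishes is that the data choose between a comparison of means and one of ranks, that the rank branch and the limit on intervals leave no unadjusted mean-difference interval for the margin, and that no single TNSS analysis is declared primary. That the rank branch may well be reached follows from the scale and the entry rule. The simulated frequencies depend on assumed means, SDs and test, and are not predictions.

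The benefit of baseline adjustment is a range: about 2 points of pairwise power at r = 0.2, 4 at r = 0.3 and 10 at r = 0.5, with the 0.5 SD margin taken in day-28 SD units and 64 analysed per arm. No single figure should be given for the comparison with change scores, because k is unknown. None of this shows that the trial is underpowered or that its unadjusted comparison is biased.

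**What to change.** 1. Name one primary analysis: ANCOVA of day-28 TNSS on treatment arm and baseline TNSS, used regardless of any normality check, with a bootstrap confidence interval as sensitivity analysis. Naming day 28 also settles what the end of the study means here, since the Primary outcome section lists three post-baseline times.
2. From that model report a confidence interval for each test arm minus loratadine and compare it with the margin, expressed in points on the original TNSS scale. Do not rescale 0.5 SD to the smaller residual SD, because that would cancel the gain in power.
3. Remove the normality-dependent switch for TNSS. Keep end-value, change and rank analyses as supportive only.
4. Use the same model for each continuous secondary outcome, with its own baseline value as covariate. List any further covariates in advance and justify them as prognostic.

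**Cost.** This is a change of wording and one degree of freedom; the data are already being collected. Recruitment was in progress at publication, and the Ethical considerations section sends protocol modifications to the ethics committees and the registry, so the change should be notified there before the data are analysed.

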**Study design:**

This is a three-arm, open-label, non-inferiority, randomized controlled clinical trial enrolling patients with AR. Tamalakyadi decoction containing 12 ingredients (TMD12), used in traditional Ayurveda and its freeze-dried formulation are the test products. The efficacy and safety of the two Ayurvedic dosage forms will be tested against the antihistamine loratadine. Patients with symptoms of AR will be allocated randomly into the three arms after a 1-week run-in period and the medications will be given orally for 28 days. Total Nasal symptom Score (TNSS) of the patients will be used as the primary efficacy endpoint. TNSS will be recorded and compared between the three arms prior to visit 1, at the end of 28 days, and end of the first and second months of follow-up. Symptom scores of daytime nasal symptoms, night time nasal symptoms, non-nasal symptoms and health-related quality of life questionnaire are used as secondary end points.

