### Recruitment

People who are interested in participating in this clinical study will be provided with a detailed Patient Information Leaflet (PIL) supplemented by verbal explanation of the study procedures. If the participants agree with the information given in PIL, the screening questionnaire will be completed. Informed written consent will be obtained from each participant by the investigators prior to initial interview. The activities in the initial interview will include complete history taking, physical examination, and hematological and biochemical investigations (IgE level, FBS, FBC, ESR, ALT/AST, serum creatinine, UFR). Diagnosis of allergic rhinitis will be made according to the Allergic Rhinitis and its Impact of Asthma (ARIA) criteria. Among them, the participants meeting the inclusion and exclusion criteria will be recruited for the study. All baseline assessment forms (Total Nasal Symptom Score, Quality of life questionnaire and allergic rhinitis symptom score) will be completed by the investigators. Patients will not be allowed to take any other medicines during the trial period. If they have to take any other medicine, they should inform the investigators and discontinue the trial.

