#### Secondary outcomes

The following four symptom scores will be used as secondary end points.
Mean score of daytime nasal symptomsMean score of night time nasal symptomsMean score of non-nasal symptomsPatient’s self-rated symptom scores (daily rhinitis diary card) and allergic rhinitis grading symptoms will be used as secondary measures of the efficacy in the clinical trial. Such symptom scores will be collected on a weekly basis during the assessment period. The measurement of symptoms on a four-point rating scale with the following definitions will be used.
= absent symptoms (no signs/symptoms evident)= mild symptoms (signs/symptoms clearly present, but minimal awareness; easily tolerated)= moderate symptoms (definite awareness of signs/symptoms that are bothersome but tolerable)= severe symptoms (signs/symptoms that are hard to tolerate; causes interference with activities of daily living and/or sleep).Mean score of health-related quality of life score – Health-related quality of life is measured using allergic rhinitis symptoms at the baseline and end of the intervention (after 4 weeks, 1 month of follow-up, and 2 months of follow-up).

Changes in the serum IgE level and eosinophil count will be studied by comparing before and after treatment values. Procedures related to the study are shown in Table 2.

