#### Safety assessment

Each patient will undergo hematological and biochemical investigations (FBS, FBC, ESR, AST/ALT, and serum creatinine/GFR), urine full report before and after the interventions, which are done primary for safety assessment.

All adverse events experienced by patients will be recorded weekly by the investigators at every visit to the clinic. Further, patients will be advised to record any adverse reactions in their patient diaries and will be advised to inform the investigators using the given contact numbers. They will also be advised to come to the clinic for assessment when they have any unexpected symptoms or complaints. If any serious adverse events occur, they will be carefully assessed and reported to the ERC of IIM and Medical Faculty within 5 working days. No serious adverse reactions are expected with any of the three study medications. However, in the events of an adverse reaction requiring in-hospital management, the facilities and expert management would be provided and the complete clinical trial will be terminated prematurely if there is evidence that the safety of the trial participants can no longer be assured or new scientific information arises during the course of the clinical trial regarding patient safety.

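### Last-value carry-forward can enter baseline TNSS as the day-28 result of early leavers; the direction of the bias depends on relative dropout

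*Protocol article*

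**What the plan says.** All references are to the protocol article.

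- **Missing-data rule** (Method of data analysis): "Missing data at outcome assessment will be replaced with the available latest values of the outcome measure".
- **Main analysis set** (same section): "Intention-to-treat analysis will be performed for all efficacy outcomes and safety outcomes".
- **Second analysis set** (same section): the article also plans an analysis restricted to completers, for efficacy alone: "per-protocol analysis will be performed for the efficacy outcomes by including only the patients completing the follow-up". It does not say which set decides the non-inferiority question.
- **TNSS schedule** (Abstract, Study design): "TNSS will be recorded and compared between the three arms prior to visit 1, at the end of 28 days", and then at the ends of the first and second follow-up months. The Primary outcome section gives the same four time points.
- **Weekly data** (Secondary outcomes): "Such symptom scores will be collected on a weekly basis during the assessment period". This refers to the secondary symptom scores, not to TNSS.
- **Leaving the trial** (Recruitment): patients may take no other medicine. "If they have to take any other medicine, they should inform the investigators and discontinue the trial". No later data collection is described.
- **Safety laboratory tests** (Safety assessment): blood tests and "urine full report before and after the interventions, which are done primary for safety assessment". Adverse events are handled separately: "All adverse events experienced by patients will be recorded weekly by the investigators at every visit to the clinic".

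**The concern.** On the stated schedule, the only TNSS available before day 28 is the baseline value. For anyone who leaves during treatment, the latest available value is therefore pre-treatment, and the rule scores that patient as unchanged. The discontinuation rule produces such leavers, plausibly for reasons linked to symptoms.

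In a non-inferiority trial this is not a neutral choice. Giving the same zero to leavers in every arm pulls the arms together, which makes a truly inferior product look closer to loratadine. Unequal dropout adds a second effect: the arm that loses more patients collects more zeros. The error rate of the non-inferiority claim then depends on who leaves, and the intention-to-treat label does not protect against that.

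There is a narrower safety question. Laboratory tests are done once before and once after treatment. If the rule is read to cover them, an early leaver's pre-treatment result would stand in for the missing one and show no change.

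**Working it through.** **1. The plan's own figures (Sample size).** Inputs: margin 0.5 SD, alpha 5%, power 80%, 64 per group, 10% dropout, 70 per arm.

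n = 2(1.96 + 0.842)² / 0.5² = 62.8, so 63. The t-based version gives 63.8, so 64 as stated. A one-sided 5% test gives about 50 and does not reproduce the figure. The nominal false non-inferiority rate is therefore taken as 2.5%. For dropout, 64 × 1.1 = 70.4 and 63 / 0.9 = 70, both consistent with the stated 70 (64 / 0.9 would give 72).

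**2. Model for carry-forward from baseline.** Work in SD units of the TNSS change. Let m be the true mean improvement on loratadine, δ the true deficit of the test product, and d_L and d_T the proportions lost before day 28. Leavers get change 0.

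- Loratadine mean: (1 − d_L)m. Test mean: (1 − d_T)(m − δ).
- Variance in an arm with dropout d and true mean μ: (1 − d)(1 + μ²) − [(1 − d)μ]².
- Non-inferiority is declared if the upper 95% limit for the difference is below 0.5, with 70 per arm.

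Assumptions not in the article: m from 0.5 to 2; all dropout before day 28; no TNSS between baseline and day 28; leavers would otherwise have responded like completers in their arm; margin held at 0.5 of the completers' SD.

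**3. One case in full.** m = 1, δ = 0.5, 10% lost in each arm.

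- Means: 0.9 × 1 = 0.90 and 0.9 × 0.5 = 0.45. The apparent deficit is 0.45.
- Variances: 0.9 × 2 − 0.81 = 0.99 and 0.9 × 1.25 − 0.2025 = 0.9225.
- SE = √[(0.99 + 0.9225)/70] = 0.165.
- False non-inferiority rate = Φ[(0.5 − 0.45)/0.165 − 1.96] = 4.9%.

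**4. False non-inferiority rate when the true deficit equals the margin.**

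| Lost before day 28 (loratadine / test) | Apparent deficit, SD (m = 0.5 to 2) | m = 0.5 | m = 1 | m = 1.5 | m = 2 |
|---|---|---|---|---|---|
| 0% / 0% | 0.50 | 2.5% | 2.5% | 2.5% | 2.5% |
| 10% / 10% | 0.45 | 5.0% | 4.9% | 4.7% | 4.6% |
| 20% / 20% | 0.40 | 9.6% | 9.1% | 8.3% | 7.5% |
| 15% / 5% | 0.425 to 0.275 | 6.7% | 11.3% | 16.9% | 22.7% |
| 5% / 15% | 0.475 to 0.625 | 3.6% | 1.7% | 0.8% | 0.4% |

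A simulation at 10% / 10% (40,000 runs, loratadine improvement 3-5 points, SD 2.5-3) gave 4.4-5.0%, in line with the second row.

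**5. Where the direction turns.** The apparent deficit is back at 0.50 when d_L·m = d_T(m − 0.5). With d_L = 10%, that is d_T = 20% at m = 1, 15% at m = 1.5 and 13.3% at m = 2. Beyond those values the bias runs against non-inferiority. At m = 0.5 the inferior product has no true improvement to lose, so there is no reversal.

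**6. Power when the products are truly equal.** With no dropout it is 84.1%. With 5% / 15% it is 79.2%, 66.3%, 50.7% and 35.5% for m = 0.5, 1, 1.5 and 2.

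**The case against.** Much of the case on the other side stands.

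- **Direction.** A reader might infer that the rule always favours non-inferiority. It does not: it penalises whichever arm loses more patients, as the last row of the table shows.
- **Size.** A reader might also assume heavy loratadine dropout, because the trial is open-label at an Ayurveda hospital and the Discussion says some patients prefer herbal remedies. With 20% lost on loratadine and 10% on test, simulation gives 15-25%; with 25% and 10% it gives 23-44%. The article does not support singling out those scenarios. Its only dropout figure is 10%. The Background section describes daily decoction preparation as a burden, and the Product I section asks patients to simmer 1920 ml down to 240 ml every day, against one tablet for loratadine. That is a reason for more dropout on the decoction. A truly inferior product may also drive more of its own patients to other medicine. In the mirror case, 10% on loratadine and 20% on test, simulation gives 0.6-2.5%.
- **Safety.** A reader might infer that the rule hides toxicity. The rule does not name laboratory values; covering them is an inference from the next sentence, which applies intention-to-treat to safety outcomes. Adverse events are recorded weekly and in diaries, and a data safety monitoring board is in place. None of this depends on the post-treatment sample.
- **Schedule.** Table 2 is not visible, so weekly TNSS cannot be excluded. If it is scheduled, the carried value is a partial response. The bias shrinks but does not vanish.
- **Per-protocol analysis.** It is largely free of carried-forward baselines. However, it keeps only patients who completed follow-up, so it selects on the same dropout, and it is not named as decisive. It does not rescue the rule.

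An unseen statistical analysis plan is no answer to the main point, because the article states the method rather than leaving it open.

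**Conclusion.** The concern holds as a flaw in a stated method. On the visible schedule, early leavers can enter the day-28 intention-to-treat comparison with baseline TNSS counted as an observed result. At the planned 10% dropout, equal across arms and all before day 28, a 0.50 SD deficit appears as 0.45 SD and the false non-inferiority rate roughly doubles, from 2.5% to about 4-5%. More dropout on loratadine raises it further. Clearly more dropout on a test arm generally reverses the bias and can cost considerable power. These figures rest on the assumptions listed in the working, above all that no TNSS is taken between baseline and day 28.

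For safety, the supportable statement is limited: if the rule covers laboratory values, it would show no change in early leavers. Weekly adverse event recording is unaffected. Patients who leave after day 28 are a different case, since the value carried into follow-up is then the day-28 score, not a pre-treatment one.

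**What to change.** 1. Replace the carry-forward sentence with multiple imputation or a likelihood-based repeated-measures model that uses baseline TNSS, arm and the weekly symptom scores. The weekly scores must actually enter the model: on the visible schedule, a model of TNSS alone has no post-baseline information on early leavers.
2. Add a sensitivity analysis that worsens imputed test-arm values in steps up to the margin, and report whether the non-inferiority conclusion survives.
3. Report laboratory values as observed, with no carry-forward.
4. State that patients who stop study treatment are still asked for day-28 TNSS, adverse events and laboratory tests. Reword the Recruitment sentence so that stopping study treatment and leaving follow-up are separate events. The clinical rule on other medicines need not change.

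The cost is a protocol amendment, some extra analysis, and contact with patients who stop. The weekly scores are already collected, and the weekly reminder contacts described in the Product III section can be used for this.
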